#### Primary outcomes include:

PTSD Checklist for DSM-5 (PCL-5): Primary outcome measure assessing PTSD symptoms. Indonesian version Cronbach’s α = 0.93

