**Secondary outcomes include:**

Connor-Davidson Resilience Scale (CD-RISC-25)WHO Quality of Life-BREF (WHOQOL-BREF): Assesses physical, psychological, social, and environmental quality of life. Cronbach’s α range: 0.41–0.77

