### Sample size

A priori power analysis using G*Power 3.1 estimated a required total sample size of 207 participants (138 intervention, 69 control) to detect a medium effect size (Cohen’s d = 0.5), with α = 0.05, power = 0.80, and accounting for 30% attrition.

The choice of medium effect size (d = 0.5) is based on prior meta-analytical findings from studies evaluating SE® and other body-oriented trauma interventions among individual PTSD or complex trauma symptoms. Specifically, Payne et al [7] and Andersen et al [16–18] report medium to large effect sizes in PTSD symptom reduction following SE® informed interventions. Given the cultural adaptation and group-based format in this study, a conservative medium effect size was deemed appropriate.

Participants will be randomized in a 2:1 allocation ratio using block randomization generated through Castor EDC software.

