### Statistical analysis plan

All statistical analyses will be performed using SPSS version 22.0.

Descriptive statistics will be used to summarize demographic and clinical characteristics of the participants.Baseline differences between groups will be examined using chi-square test for categorical variables and t-test for continuous variables.To evaluate treatment effects, linear mixed-effect models will be used to analyse the interaction of time (T0, T1, T2, T3) and group condition (intervention vs control) on primary and secondary outcomes.The models will include fixed effects for time, group, and time x group interaction, and random intercepts for participants to account for within subject variability across time points.To minimize confounding related to unequal treatment exposure, total professional contact time (minutes) within and outside the study will be logged for each participant. In prespecified secondary analyses, this variable will be included as a covariate in the mixed-effects models. Additional sensitivity analyses will be conducted, including (i) exclusion of participants who receive substantial trauma-focused services outside the protocol, (ii) per-protocol analyses restricted to participants with adequate adherence (≥ 80% of assigned sessions), and (iii) exploratory dose-response models testing the interactions between group assignment and contact time. These steps will allow us to assess whether intervention effects remain robust after adjusting for variation in professional contact time.Effect sizes will be reported using Cohen’s d.All analyses will follow the intention-to-treat (ITT) principle, including all randomized participants. Missing data will be handled using regression imputation under the assumption that data are missing at random (MAR). Specifically, predictive mean matching will be used to impute missing continuous outcome variables, which is considered appropriate for longitudinal clinical trial data.

To control for the increased risk of Type I error due to multiple comparisons across outcomes, A Bonferroni correction will be applied.

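### The Bonferroni rule across outcomes does not exempt the single primary outcome, PCL-5, although the sample size of 207 gives that test the undivided alpha of 0.05

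*Protocol article*

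**What the plan says.** Under Primary outcomes, one instrument is listed, the PCL-5, described as "Primary outcome measure assessing PTSD symptoms". Under Secondary outcomes there are two instruments: CD-RISC-25 and WHOQOL-BREF. The second of these "Assesses physical, psychological, social, and environmental quality of life", so it can be analysed as one score or as four domains.

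The Sample size section rests on a G*Power calculation for a standardised difference of 0.5 and arrives at 207 participants, split 138 and 69. The error rates and the allowance for losses are given there as follows: "with α = 0.05, power = 0.80, and accounting for 30% attrition". It does not divide alpha for multiple outcomes.

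The Statistical analysis plan section applies linear mixed models with a time-by-group interaction to the primary and the secondary outcomes alike. It ends with the multiplicity rule: "To control for the increased risk of Type I error due to multiple comparisons across outcomes, A Bonferroni correction will be applied". The section does not say which outcomes form the family, how many tests there are, or whether PCL-5 stands outside the correction.

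**The concern.** The only outcomes that the analysis section names are the primary and secondary ones together. A correction across outcomes therefore most naturally includes PCL-5, and PCL-5 would be tested at 0.05 divided by the number of outcomes. The sample size calculation assumes that it is tested at 0.05. The two statements do not describe the same test.

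Two things are at stake. First, the stated 80% power would not belong to the primary test as planned. Second, the success criterion is open: a PCL-5 p-value of 0.03 is a positive trial at 0.05 and a negative one at 0.025, 0.0167 or 0.0083. As the text stands, that choice could be made after the data are seen.

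**Working it through.** **Inputs from the protocol.** d = 0.5, alpha = 0.05, power 0.80, 30% attrition, 138 + 69 = 207 (Sample size). "Participants will be randomized in a 2:1 allocation ratio using block randomization" gives the 2:1 ratio. Sidedness is not stated.

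**Step 1: reproduce 207.** For two means with a 2:1 ratio, the control-arm size is

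n = (1 + 1/2) × (z for alpha + z for power)² / d².

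Two-sided at 0.05: 1.5 × (1.960 + 0.842)² / 0.25 = 47.1, so 48 control and 96 intervention, 144 evaluable. The noncentral t calculation also gives 48. Attrition: 48 / 0.7 = 68.6, so 69 control, 2 × 69 = 138 intervention, total 207. This matches exactly. A one-sided test would need 38 control: 38 / 0.7 = 54.3, so 55, and 3 × 55 = 165. The figure of 207 therefore rests on a two-sided, undivided alpha of 0.05.

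**Step 2: choose divisors.** The protocol gives none, so these are assumptions:
- 3: PCL-5, CD-RISC-25 and WHOQOL-BREF as one score.
- 6: PCL-5, CD-RISC-25 and four WHOQOL-BREF domains.
- 2: shown as a milder case.

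**Step 3: power at the divided alpha.** The noncentrality is 0.5 × √(96 × 48 / 144) = 0.5 × √32 = 2.828, with 142 degrees of freedom.

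| Divisor | Alpha | Critical t | Power |
|---|---|---|---|
| 1 | 0.05 | 1.977 | 80.2% |
| 2 | 0.025 | 2.265 | 71.3% |
| 3 | 0.0167 | 2.423 | 65.8% |
| 6 | 0.0083 | 2.676 | 56.2% |

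**Step 4: size needed to keep 80% with PCL-5 in the family.** With 3 tests, 64 + 128 evaluable; 64 / 0.7 = 91.4, so 92 + 184 = 276 randomised. With 6 tests, 74 + 148 evaluable; 74 / 0.7 = 105.7, so 106 + 212 = 318.

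**Step 5: sensitivity.**

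*Attrition.* If all 207 were evaluable, power would be 83.5% with 3 tests and 76.6% with 6.

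*Model.* The planned test is a time-by-group interaction, not a single two-sample comparison. As a rough guide, take a baseline-to-follow-up change contrast. If d = 0.5 is scaled to the SD of one measurement and r is the within-person correlation, the effective d is 0.5 / √(2(1 − r)). The protocol gives no r, so a range is shown, with 96 + 48 evaluable:

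| r (assumed) | Effective d | Power at 0.05 | Power at 0.0167 | Power at 0.0083 |
|---|---|---|---|---|
| 0.3 | 0.423 | 66% | 49% | 39% |
| 0.5 | 0.500 | 80% | 66% | 56% |
| 0.6 | 0.559 | 88% | 77% | 69% |
| 0.7 | 0.645 | 95% | 89% | 83% |

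The division of alpha costs power at every r, but the level and the size of the loss depend on an input that the protocol does not state.

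**The case against.** The strongest reply is that the protocol never says PCL-5 is tested at a divided alpha. A correction confined to the secondary outcomes, with the single primary outcome at 0.05, is compatible with the multiplicity sentence and agrees with the Sample size section. On that reading power stays at 80% and 207 is sufficient on its own basis. This stands as a possible reading, so the power loss can only be stated conditionally. It does not remove the point, because the sentence as written does not say so.

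A second reply is that the family and divisor are details that a condensed article may leave to a fuller analysis plan. That is fair for the divisor alone. The point here is different: a stated rule, read plainly, disagrees with a stated alpha in the same document.

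A third reply concerns the value of the rule. A reader might infer that correcting PCL-5 buys nothing. The documents do not support that. The Introduction states a three-part hypothesis covering PTSD symptoms, resilience and quality of life. Bonferroni over all outcomes controls familywise error for that set and allows a resilience or quality-of-life claim even if PCL-5 fails. It does not inflate Type I error or bias the estimates. The possible harm is lost power and an ambiguous success criterion, not a false-positive claim.

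Finally, the 66% and 56% come from a two-sample t-test, not from the planned mixed model, and they assume the full 30% attrition. Both limits stand.

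**Conclusion.** The inconsistency is real. The trial is sized for PCL-5 at two-sided 0.05, while the multiplicity rule, read plainly, tests PCL-5 at something smaller. On the protocol's own sample-size basis, power would be about 71%, 66% or 56% for divisors of 2, 3 or 6, against the stated 80%.

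This rests on three assumptions: PCL-5 lies inside the corrected family; the divisor is one of those values; and the two-sample basis with 96 + 48 evaluable is the relevant one.

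A reader might go further and conclude that the trial's power simply is 66% or 56%, or that 207 is too small. The documents do not support that: they give neither a divisor nor a within-person correlation, and a secondary-only correction would leave the power at 80%.

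**What to change.** Replace the multiplicity sentence with a rule to this effect: PCL-5 is tested at two-sided 0.05; the multiplicity correction (Bonferroni or Holm) applies to the secondary outcomes, which are tested for confirmatory claims only if PCL-5 is significant. State whether WHOQOL-BREF counts as one test or four, so that the secondary family is 2 or 5 tests. The primary test then has the alpha for which the trial was sized, and 207 needs no change on its stated basis.

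The cost is a sentence or two before data are analysed. The small downside is that no confirmatory claim on resilience or quality of life can be made if PCL-5 is not significant.

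If the sponsor prefers to keep PCL-5 in the Bonferroni family, the protocol should state the divisor and restate the power at the corrected alpha: about 66% for 3 tests or 56% for 6 on its own basis. Keeping 80% would instead require about 276 or 318 randomised.

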### Monitoring

As this is a minimal risk behavioral trial, no formal data monitoring committee (DMC) will be established. Oversight will be provided by a senior clinical psychologist independent from the intervention facilitators. No interim analyses are planned. The trial may be stopped early by the principal investigator or the ethics committee in the event of safety or ethical concerns.

SE® practitioners will monitor participant safety through pre- and post-session grounding, and report any adverse events to the university ethics board. Internal auditing will be conducted every three months by the Department of Clinical Psychology’s research ethics monitoring team, which operates independently from the investigators.

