### Intervention

#### Group-based SE® Intervention.

Participants in the intervention arm will attend 10 weekly group sessions (3 hours/session) of manualized, group-based SE® intervention based on SE® principles. The intervention emphasizes bottom-up processing of trauma, stabilization of the autonomic nervous system, and completion of incomplete defensive responses. A Module Structure of Group-based SE® sessions is presented in Table 1.

**Table 1 pone.0336956.t001:** Module Structure of Group-based SE® sessions.

No	Module Title	Content/Activities	Intention	Target Issues	Skill Taught	Homework	Supplies
1	Preparatory 1	• Welcome and Introduction • Facilitator greeting, acknowledging courage to attend • Icebreaker: each participant states their name and one personal resource • Building cohesion and safety • Orientation exercise • Group agreement: • Psycho- education: Introduce SE**®** and PTSD • Brief explanation of trauma as incomplete defensive responses • Importance of body-based approaches and group support. • How SE**®** group can help • Experiential Exercise: • Guided practice • Invite sharing • Normalize varied responses • Integration and Group Agenda • Reflection • Collect and record group goals • Emphasize collaborative ownership process • Closing •Summarize today’s agenda • Introduce homework • Closing ritual: each participant shares one word/gesture for how they leave the session	• Build group cohesion and establish a sense of safety. • Orient participants to group purpose, structure and rules. • Introduce SE® and its relevance to PTSD recovery • Facilitate gentle re-connection to bodily sensation and resources	• Relational safety and trust. • Disconnection from the body and avoidance of interoception • Uncertainty about group role, expectations, and confidentiality • Normalization and universality (reducing isolation).	• Grounding and orienting in the present moment. • Identifying and using internal and external resources. • Sensation tracking (pleasant, neutral, unpleasant). • Respectful communication and group process skills.		• Name cards • Sensation name cards • SE®PowerPoint

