### Intervention fidelity and monitoring

Each group-based SE® session will be delivered by trained SE® practitioners and supervised by a senior clinical psychologist. At the end of each session, participants will complete:

**Session Rating Scale (SRS)** for therapeutic alliance**Helpful Aspects of Therapy (HAT)** form for qualitative feedback

Grounding exercises will be conducted before and after each session to promote emotional regulation.

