### Treatment As Usual (TAU)

Participants in the control arm will receive five group counselling sessions (90minutes per session) over five weeks. These sessions focus on psychoeducational counseling session, covering basic mental health support strategies and coping techniques, and are facilitated by licensed psychologist. The decision to provide five 90 minute per sessions is based on evidence from Indonesian research and practice, which showing that survivors of sexual assault typically receive between 4–7 session of psychological support(Ayudia et al. 2025c; Sumekar and Sunawan 2019).

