#### Outcome Measures and Timing.

Outcomes will be measured at four time points:

**T0**: Baseline (Week 0)**T1**: Post-treatment (Week 10)**T2**: 1-month follow-up (Week 14)**T3**: 3-month follow-up (Week 22)

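### The stated adverse-event rule names a reporter and a method that belong to the SE® sessions, so discrete harms are ascertained unequally between the arms

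*Protocol article*

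**What the plan says.** The article has one sentence on who looks for and reports adverse events, in the Monitoring section: "SE® practitioners will monitor participant safety through pre- and post-session grounding, and report any adverse events to the university ethics board". It fixes three things: the reporter, the occasion and the recipient.

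The section on intervention fidelity says where these staff work: "Each group-based SE® session will be delivered by trained SE® practitioners and supervised by a senior clinical psychologist". It adds, for the same sessions, "Grounding exercises will be conducted before and after each session to promote emotional regulation". The Recruitment and setting section also has SE® practitioners guide the grounding that opens each session.

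The Treatment As Usual section describes the other arm: "Participants in the control arm will receive five group counselling sessions (90minutes per session) over five weeks". The sessions cover psychoeducation and coping, "and are facilitated by licensed psychologist". It mentions neither grounding nor a duty to report adverse events.

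On assessments, the article says "Outcomes will be measured at four time points", the last being the "3-month follow-up (Week 22") visit.

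**The concern.** A comparison of harms between arms is interpretable only if events are looked for in the same way in both. Here the text ties ascertainment to a profession and a procedure that belong to one arm. This is a printed rule, not mere silence, and a site that follows it exactly will collect harms unequally.

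The trial is meant to inform policy and scale-up of a group trauma therapy, so readers will ask whether the therapy unsettles participants more than usual care does. If events are sought in one arm and arrive only by chance in the other, the counts cannot answer that. Events missed during the trial are hard to reconstruct afterwards. The PCL-5 primary analysis is not affected.

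**Working it through.** The plan gives no adverse-event figure to reproduce. The check is a reading of the text, followed by simple arithmetic on how large the asymmetry is.

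**Step 1: does another provision give the control arm an adverse-event reporter?**

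| Provision (section) | What it does | Assigns adverse-event reporting? |
|---|---|---|
| Independent senior psychologist (Monitoring) | General oversight | No |
| Three-monthly audit (Monitoring; Auditing) | Ethical and methodological compliance | No |
| Facilitator notices marked distress (Discontinuation criteria, under Intervention) | Referral | No |
| Support after the trial (Ancillary and post-trial care) | Support and referral | No |
| Weekly contact by research assistants (Participant retention and follow-up) | Retention and reminders | No |
| Licensed psychologist (Treatment As Usual) | Runs the control sessions | No |
| SE® practitioners (Monitoring) | Monitor safety and report | Yes, around session grounding |

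Only the last row assigns the task.

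**Step 2: size of the asymmetry, from the article's own figures.**
- Women without a named reporter: 69 of 207 = 33%.
- SE® schedule: "Participants in the intervention arm will attend 10 weekly group sessions (3 hours/session"), so 10 × 180 = 1,800 minutes under the named route.
- Control schedule: 5 × 90 = 450 minutes, none of it under the named route.
- Ratio of session time: 1,800 / 450 = 4.

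The last ratio matters for the remedy. If control facilitators were given the same duty, session-based reporting would still observe SE® women for four times as long, and over ten weeks instead of five. A question asked at the same visits in both arms does not have that problem.

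**Step 3: what unequal capture does to the counts.** Let p be the true event risk, assumed equal in both arms, and c the fraction of events captured in an arm. Expected reports are 138 × p × c(SE®) and 69 × p × c(TAU). The apparent risk ratio is c(SE®) / c(TAU), whatever p is. The documents give neither p nor c. Both are assumptions, shown over a range:

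| p | SE®, c = 1 | SE®, c = 0.5 | TAU, c = 1 | TAU, c = 0.5 | TAU, c = 0.25 |
|---|---|---|---|---|---|
| 5% | 6.9 | 3.45 | 3.45 | 1.73 | 0.86 |
| 10% | 13.8 | 6.9 | 6.9 | 3.45 | 1.73 |
| 20% | 27.6 | 13.8 | 13.8 | 6.9 | 3.45 |

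Full capture under SE® and half under TAU gives an apparent ratio of 1 / 0.5 = 2 with no true difference. Half under SE® and full under TAU gives 0.5.

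**Step 4: direction.** Active reporting in one arm alone would tend to make SE® look worse. But the reporters also deliver the therapy and know the allocation, and session 6 in Table 1 teaches that trembling, shaking and heat are signs of recovery. Some SE® events might therefore not be recorded as adverse. The text does not settle which effect is larger.

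**The case against.** The strongest reply is that the sentence does not say that nobody else reports. This is a journal article. Reporter lists, forms and collection schedules usually sit in the full protocol, and their absence here is not an error. That stands for the silence on adverse-event questions at T1 to T3, and it lowers confidence in the whole point. It does not remove the point, because the article prints a specific procedure tied to one arm. If the full protocol has a wider rule, the published sentence misstates it.

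It may also be said that the Recruitment and setting section does not limit the practitioner-led grounding to one arm. But the Treatment As Usual section mentions neither those practitioners nor grounding, and Table 1 lists grounding as a skill taught in SE® session 1. Using it in control sessions would bring part of the intervention into the comparator.

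Four stronger inferences are tempting, and the document does not support them:
- **That this is the trial's only safety channel.** There is independent oversight and audit, and the principal investigator or the ethics committee can stop the trial. The sentence is only the one place where adverse-event reporting is assigned.
- **That deterioration in control women would go unrecorded.** PCL-5 is taken in both arms at every time point, by collectors blinded to allocation, and completed assessments of women who discontinue are kept. Professional contact outside the study is also logged for each participant.
- **That late harms would be unseen in both arms.** PCL-5 runs to week 22, so symptom worsening is visible. For discrete events after the sessions, the article is merely silent.
- **That the plan will produce a false significant harm signal.** Under full SE® capture and no control capture at an assumed 10% risk, 14/138 against 0/69 gives a two-sided Fisher p of about 0.006. Two captured control events raise it to about 0.096, and three to about 0.19. The rates and capture fractions are invented, and the statistical analysis section plans no such test.

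**Conclusion.** The point holds in a limited form, with medium confidence. As written, the rule actively ascertains discrete adverse events in the SE® arm and gives no equivalent for the 69 control women (33% of those randomised). A statement on safety by arm would carry ascertainment bias of uncertain direction. Its size cannot be derived from the document. With equal true risk, the apparent risk ratio equals the ratio of the capture fractions.

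This rests on two assumptions: that SE® practitioners and session grounding belong to the SE® arm, which is the natural reading, and that the full protocol does not assign further reporters. The harms concerned are crises, self-harm and similar events, not PTSD symptom worsening. The change should be made before recruitment, planned for January 2026, but it does not threaten the primary result.

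**What to change.** Replace the sentence in Monitoring with one rule for both arms:
- SE® practitioners and control-arm facilitators report adverse events to the university ethics board on the same form.
- The same short adverse-event question is added to the existing T1, T2 and T3 assessments for every participant, whatever her arm or attendance. It should not ask about session content, so that the data collectors stay blinded.
- Events are tabulated descriptively by randomised arm, with no formal test.

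If the full protocol already says this, only the published sentence needs correcting. The cost is one sentence, one form and one question in the existing REDCap set-up, and a little more reporting work. The facilitators and data collectors are already part of the plan. The sample size and the primary analysis do not change.
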